**Gait:**

- **12** walks 5 m without aids
- **9** walks with aids
- **6** walks with help of another person
- **3** sits without support
- **0** bedridden/wheelchair

**Stroke Oxygen Study**

# Day 3 Assessment (Assessment form 1)

Name Randomisation no

Pulse oximetry night 2 21:00-9:00 complete Yes No

If pulse oximnetry is not complete, repeat on night 3

Compliance with treatment regimen (tick the statement that applies on day 3)

| Oxygen currently in place (2) | Oxygen not in place, but patient and staff report that the patient is receiving oxygen (1) | No evidence of oxygen supplementation  (0) |
| --- | --- | --- |

Medical History (circle yes or no as appropriate)

| COAD or Asthma [by Hx or from list of drugs] | YES | NO |
| --- | --- | --- |
| Other chronic lung problem [kyphoscoliosis, thoracoplasty, pneumoconiosis etc) | YES | NO |
| Heart failure [by Hx or >20 mg frusemide or equivalent per day] | YES | NO |
| Ischaemic heart disease [H/O angina or MI or tx with nitrates or nicorandil] | YES | NO |
| Atrial fibrillation | YES | NO |

Stroke classification (circle the class that reflects the patient's worst symptoms)

| TAC | PAC | LAC | POC | TIA | Unclassifiable |
| --- | --- | --- | --- | --- | --- |

| Date of pulse oximetry |  |
| --- | --- |
| Baseline wake oxygen saturation |  |
| Mean nocturnal oxygen saturation |  |
| The 4% Oxygen Desaturation Index |  |
| The lowest nocturnal oxygen saturation |  |
| The time spent with an oxygen saturation <95% |  |
| The time spent with an oxygen saturation <92% |  |
| The time spent with an oxygen saturation <90% |  |
| The time spent with an oxygen saturation <80% |  |
| The time spent with an oxygen saturation >98% |  |
| The mean nocturnal heart rate |  |

**Stroke Oxygen Study**

**Week 1 (Assessment form 2 a)**

Name Randomisation no

Date of death (if applicable)

Please complete the Notification of Death Form if the patient is deceased.

| Antibiotics prescribed since admission | YES | NO |
| --- | --- | --- |
| Continuous oxygen prescribed outside protocol for clinical indications | YES | NO |
| Sedatives or antipsychotic drugs prescribed since admission | YES | NO |
| Highest temperature during week 1 |  |  |
| **The highest heart rate during the 3 days of trial treatment** |  |  |
| **The highest systolic blood pressure during the 3 days of trial treatment** |  |  |
| **The highest diastolic blood pressure during the 3 days of trial treatment** |  |  |
| Highest temperature during week 1 |  |  |

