**DETAILED PLAN OF INVESTIGATION**

**Summary of the study**

This is a study of the effect of routine oxygen supplementation early after acute stroke. A brief synopsis of the trial structure is given in the attached Flow Chart. Subjects will be randomised to receive fixed dose oxygen or no routine oxygen for 72 hours. Oxygen saturation will be recorded over night by pulse oximetry on night 2. The patient will be assessed by a member of the research team on day 3 and week 1 after trial enrolment. At 3 months the researcher will consult the hospital computer system and the patient's notes to find out whether the patient was discharged from hospital and to where. At 6 months after trial enrolment the patient will be sent a questionnaire with questions relating to their daily functional abilities.

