**Recruitment**

Patients will be recruited from the University Hospital of North Staffordshire by a member of the research team or the doctor admitting the patient. Because hypoxia is more likely to be detrimental early after the stroke, when the ischaemic penumbra either recovers or expands it is crucial to include patients as soon as possible after the stroke into the trial. Patients will therefore be recruited as soon as they enter hospital via MAU or A&E, if possible, or at the next earliest opportunity up to 24 hours after admission.

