**Main outcomes**

Comparisons will be made between the treatment and control group to determine:

1. Effect size:

- Death and disability (Rankin >3) at 6 months
- Scandinavian Stroke Scale week 1
- Mortality up to 6 months
- Rankin Score at 6 months
- Nottingham EADL score at 6 months

2. Potential Side effects of the study treatment

- Rate of infections (pyrexia or antibiotic treatment at week 1)
- Agitation (sedative or antipsychotic medication at week 1)
- Physiological indicators of stress (tachycardia, hypertension)

3. To assess the feasibility of the study protocol we will examine

- Protocol violations
- Recruitment rate
- The relation between the number of recruited and excluded patients
- The percentage of completed 6-month questionnaires

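### The week 1 drug items count from admission rather than randomisation, so antibiotics and sedatives begun before allocation are scored as side effects and dilute any true difference

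*Protocol*

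**What the plan says.** The Main outcomes section lists two drug-based side-effect outcomes: "Rate of infections (pyrexia or antibiotic treatment at week 1" and "Agitation (sedative or antipsychotic medication at week 1". Neither states when the window opens.

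The data come from Week 1 (Assessment form 2 a). Its items are "Antibiotics prescribed since admission" and "Sedatives or antipsychotic drugs prescribed since admission", each a single yes/no without a start date. The fever half of the infection outcome comes from "Highest temperature during week 1", a line printed twice. On the same form the stress indicators are tied to the treatment period, for example "The highest heart rate during the 3 days of trial treatment".

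Under Recruitment, patients enter on arrival if possible, or "at the next earliest opportunity up to 24 hours after admission". The Summary of the study times the follow-up visits "on day 3 and week 1 after trial enrolment". Neither the Randomisation Form nor the medical history on the Day 3 form has a field for antibiotics, sedatives or antipsychotics in use at randomisation.

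**The concern.** The outcome window opens up to a day before treatment is allocated. An antibiotic begun on arrival, or a sedative given or re-prescribed in the admissions unit, cannot be an effect of the allocation, yet it is scored as one. The form is also inconsistent with itself: heart rate and blood pressure are tied to trial treatment, while the drug items are tied to admission.

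Side effects are one of the pilot's main objectives, and confusion, restlessness and infection are named there. Pre-randomisation prescriptions fall equally on both arms in expectation, so they add the same background to each and make the arms look more alike. In a screen for harm, that error leans towards false reassurance. The pilot is also meant to inform the multicentre trial, which could inherit the diluted estimate.

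An analysis plan cannot settle this, because no trial form collects the dates or the status at randomisation that a correction would need.

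**Working it through.** **The plan's own figures.** The protocol gives no event rate, effect size or power for infection or agitation. Its only power statement (Study size) is for 0.4 SD on the functional outcomes at 90% power and two-sided 5%. That needs 2 × (1.960 + 1.282)² / 0.4² = 131.3, so 132 per arm. The planned 150 give about 93%, so the statement is conservative and does not bear on this point.

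**Inputs.**
- From the protocol: 150 per arm; up to 24 hours from admission to randomisation; drug items counted from admission.
- Assumed: true rates after randomisation of 20% (control) and 30% (oxygen); a share q already on the drug at randomisation, equal in both arms, taken as 2%, 5%, 10% and 20%. Two-sided 5% is carried over from Study size.

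**Recorded rates.** With true later rate p, the form records q + (1 − q)p. The recorded risk difference is therefore (1 − q) times the true one, and the risk ratio moves towards 1.

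**Power.** This is the normal approximation for two proportions: Φ[(d − 1.96 × SE0) / SE1], with SE0 from the pooled rate and SE1 from the separate rates.

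Example at q = 10%:
- Control: 0.10 + 0.90 × 0.20 = 0.28. Oxygen: 0.10 + 0.90 × 0.30 = 0.37.
- Risk ratio: 0.37 / 0.28 = 1.32. Difference d = 0.09.
- SE0 = √(0.325 × 0.675 × 2/150) = 0.0541.
- SE1 = √((0.28 × 0.72 + 0.37 × 0.63)/150) = 0.0538.
- Power = Φ[(0.09 − 0.1060)/0.0538] = Φ(−0.30) = 38%.

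**What the fix recovers.** There are two ways to count only new starts:
- (a) Keep everyone in the denominator and count no further start in those already treated. The rates are (1 − q) × 20% and (1 − q) × 30%, with 150 per arm.
- (b) Leave out those already treated. The rates are 20% and 30%, with 150 × (1 − q) per arm.

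The ratio is 1.50 either way.

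| q | Recorded rates | Recorded RR | Power as recorded | Power after fix, (a) / (b) |
|---|---|---|---|---|
| 0% | 20.0% v 30.0% | 1.50 | 52% | 52% / 52% |
| 2% | 21.6% v 31.4% | 1.45 | 49% | 51% / 51% |
| 5% | 24.0% v 33.5% | 1.40 | 44% | 49% / 50% |
| 10% | 28.0% v 37.0% | 1.32 | 38% | 46% / 47% |
| 20% | 36.0% v 44.0% | 1.22 | 29% | 41% / 43% |

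**Sensitivity to the assumed rates.** With 15% v 30% the pattern is the same. At q = 10% the ratio falls from 2.00 to 1.57 and power from 88% to 72%; version (b) of the fix gives 84%.

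The calculation treats one drug item on its own. That matches agitation, which rests entirely on the drug item. Infection also has a fever component, which this does not model.

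**The case against.** Several points on the other side stand.

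- **Dilution is not concealment.** A reader might infer that the form hides any harm from oxygen. It does not: in expectation a true difference is weakened, not removed or reversed. At q = 10% the ratio is still 1.32.
- **The whole infection outcome is not affected.** A reader might infer that it is all recorded from admission. Only the antibiotic half is. Temperature is taken over week 1, and because the week 1 visit is timed from enrolment, the natural reading is that this window starts there too, although the form does not say so.
- **The fix does not recover 52% power.** That figure belongs to a trial in which nobody was already treated. At q = 10% the real gain is from 38% to 46–47%.
- **On the absolute scale the estimate need not change.** With everyone in the denominator, the difference at q = 10% is 9 points both as recorded (28% v 37%) and after the fix (18% v 27%). The gain there is in precision and in the ratio, and the protocol names no effect measure for side effects.
- **The share may be small.** Recruitment on arrival is the aim, and hypoxia with severe pneumonia is a listed reason for not entering a patient. If q is 2%, little is lost.
- **This is a pilot** without a formal size calculation and with no power claimed for side effects.

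These points limit the size. They do not remove the fault, because the direction of the error is known and the forms collect nothing from which q could be estimated. Other infections on arrival are not among the listed reasons for not entering a patient, and the protocol deliberately includes confused and drowsy patients, so early antibiotics or sedatives are plausible.

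**Conclusion.** The point holds as a fault in data capture. Prescriptions that the allocation cannot have caused count towards one half of the infection outcome and all of the agitation outcome. They shrink any true risk difference by the factor (1 − q).

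The direction is certain in expectation, but the size is not known: the event rates and q are assumptions, and q could differ between antibiotics and sedatives. Under 20% v 30% and 150 per arm, the loss against what the fix could recover is about 2 points of power at q = 2%, 5 to 6 at 5%, 8 to 9 at 10%, and 12 to 14 at 20%.

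The change is worth making before recruitment, since it is cheap and the missing information cannot be rebuilt from the forms afterwards. The repeated temperature line is clerical and adds no weight.

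**What to change.** - On Assessment form 2 a, reword both drug items to 'newly started since randomisation', with the start date. Add the time for drugs begun on the day of randomisation.
- Add one tick for antibiotic use and one for sedative or antipsychotic use at randomisation.
- In Main outcomes, count only new starts after randomisation. State that a new antibiotic course for a new infection counts even if the patient was already on an antibiotic at randomisation, and say whether patients already treated stay in the denominator.
- State on the form and in Main outcomes that the highest temperature runs from randomisation to day 7, and delete the duplicate line.

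The cost is a change of wording on one form, two ticks, and slightly more reading of the drug chart by the researcher. Only the recording of data changes; patient care does not.

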# STUDY DESIGN

A randomised controlled open pilot study of routine fixed dose oxygen supplementation versus no routine oxygen treatment.

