**Blinding**

This study will be open, since placebo treatment (room air via nasal cannulae) would have at least some of the side effects of active treatment (e.g. infection and immobilisation) without any potential benefit, and would thus bias the data in favour of the treatment group. The main outcomes will be ascertained at 6 months by postal questionnaire. It is likely that participants will have forgotten which treatment group they were in 6 months after the intervention, and it is therefore unlikely that treatment allocation will bias their answers. We will assess whether patients remember their treatment allocation by including this as a question in the 6 month assessment questionnaire.

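### Tachycardia, hypertension and pyrexia are captured as single highest readings in an open trial, with no common reading schedule and no count of readings, so unequal charting between arms could create or hide a harm signal

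*Protocol*

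**What the plan says.** Under Main outcomes, the protocol lists among the potential side effects "Physiological indicators of stress (tachycardia, hypertension") and "Rate of infections (pyrexia or antibiotic treatment at week 1"). It gives no cut-off for any of these signs there.

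The values are collected on the Week 1 form (Assessment form 2 a): "The highest heart rate during the 3 days of trial treatment", "The highest systolic blood pressure during the 3 days of trial treatment", the diastolic equivalent, and "Highest temperature during week 1". Heart rate and blood pressure therefore cover the three treatment days, and temperature covers the whole week. The form does not say who takes the readings, how often or at what times, and it has no entry for how many were taken.

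The Study Design section describes "A randomised controlled open pilot study of routine fixed dose oxygen supplementation versus no routine oxygen treatment". The Blinding section confirms that there is no placebo.

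Separately, the Day 3 form (Assessment form 1) records "The mean nocturnal heart rate" from oximetry run from 21:00 to 9:00 on night 2 and repeated on night 3 if incomplete. The section on overnight oximetry applies this to both arms while allocated treatment is in progress.

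**The concern.** The highest of several readings depends on two things: the patient's physiology, and how many chances there were to catch a high value. Two identical groups will differ in their maxima if one is measured more often. A comparison of maxima is therefore fair only if the number and timing of readings do not depend on the arm.

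Nothing in the protocol secures that. Staff know the allocation. The Blinding section defends openness by expecting participants to have forgotten their treatment by six months. That argument concerns the postal questionnaire and does not reach vital signs taken in the first week.

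Assessing side effects is one of the pilot's main objectives, and the section on the week 1 assessment describes this form as the screen for them. An artefact in either direction would pass into the safety case for the larger trial. The form keeps the maximum and drops the count, so an analyst working from it could not see unequal charting, let alone adjust for it.

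**Working it through.** **The plan's own figures.** The protocol gives no number for reading frequency, variability or cut-offs, so there is no figure on this point to reproduce. The only design figure used is 150 per arm (Study size). The power statement there does not bear on this point: 0.4 SD at 90% power and 5% two-sided needs 2(1.960 + 1.282)²/0.4² = 131.4, so 132 per arm, and 150 gives 93.4% power.

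**Model, with no treatment effect.** Each reading is a patient level plus within-patient variation, with total SD 1 and intraclass correlation ICC. Let m(k) and v(k) be the mean and variance of the largest of k independent standard normal values.

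- Shift in mean maximum: √(1 − ICC) × [m(k₂) − m(k₁)]
- SD of the maximum: √(ICC + (1 − ICC) × [v(k₁) + v(k₂)]/2)
- Standardised shift: d = shift/SD
- Two-sided false-positive rate at 150 per arm: Φ(d√75 − 1.96) + Φ(−d√75 − 1.96)

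**Inputs.** Reading counts and ICC (0.3, 0.5, 0.7) are assumptions. By numerical integration:

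| k | 12 | 15 | 18 | 24 | 28 | 34 |
|---|---|---|---|---|---|---|
| m(k) | 1.629 | 1.736 | 1.820 | 1.948 | 2.014 | 2.095 |
| v(k) | 0.324 | 0.301 | 0.285 | 0.262 | 0.251 | 0.238 |

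**One case in full (12 v 18 readings, ICC 0.5).** The shift is 0.707 × 0.191 = 0.135. The SD is √(0.5 + 0.5 × 0.304) = 0.807. So d = 0.167 and d√75 = 1.45. The false-positive rate is Φ(−0.51) + Φ(−3.41), about 30%.

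**Results (ICC 0.7 to ICC 0.3).**

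| Readings per patient | Shift d, in SD of the maximum | False-positive rate | Share above a cut-off that 30% of the less-measured arm exceeds |
|---|---|---|---|
| 12 v 12 | 0 | 5% | 30% |
| 12 v 15 | 0.07 to 0.12 | 9 to 19% | 32 to 34% |
| 12 v 18 | 0.12 to 0.22 | 17 to 49% | 34 to 38% |
| 12 v 24 | 0.20 to 0.38 | 40 to 90% | 37 to 43% |
| 28 v 34 (week 1 temperature) | 0.05 to 0.10 | 7 to 14% | 32 to 33% |

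The temperature row assumes six extra readings, all in the three treatment days, within a seven-day total. A simulation with 200,000 patients per setting agrees to within 0.01 SD for the shifts and 2.3 percentage points for the rates.

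The false-positive column treats the maximum as continuous. Analysed as yes/no at the 30% cut-off, the chance of a significant excess in the more-measured arm is smaller: 6 to 12% for 12 v 15 and 11 to 29% for 12 v 18, against about 2.5% with equal counts.

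**The heart-rate alternative.** A mean does not rise with the number of readings. The oximeter records automatically over the same 12 hours in both arms, so the nocturnal mean does not depend on how often staff chart.

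**The case against.** The strongest objection is that no unequal charting has been shown. A reader might infer that continuous oxygen keeps patients under closer observation, or keeps them in hospital while mild controls go home, so that the trial will overstate the harm of oxygen. The documents do not support this. The monitoring that the protocol does specify (oximetry, the day 3 and week 1 assessments) applies to both arms. No section says that treated patients are observed more often or that controls leave before day 3. The opposite is equally arguable: controls receive oxygen only if a need arises, which gives staff a reason to watch them. The direction is open.

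A reader might also take a fixed size from the fact that doubling the number of independent readings raises the expected maximum by about 0.3 within-patient SD. That figure ignores between-patient variation and rests on assumed counts. It is not an estimate for this trial.

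Three further points have weight. A maximum suits a sensitive screen, and averaging would lose the threshold events the outcomes are meant to catch. Pyrexia is the weaker limb, because its window is seven days and the infection outcome also counts antibiotics. And an SAP could supply cut-offs and choose the nocturnal mean, since Main outcomes does not exclude it.

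These points limit the direction, size and remedy. They do not remove the problem. An SAP cannot recover a reading count that was never collected. The discharge date on Assessment form 3 would let days in hospital be derived, but not how often signs were charted during those days.

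**Conclusion.** The point holds as a conditional weakness in data capture. The side-effect comparisons for heart rate, blood pressure and temperature rest on maxima, in an open trial, without a common schedule or a count. If charting frequency differs between arms, the comparison is biased against the arm measured more often, and the form would not reveal it. Equal charting gives no bias.

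Whether charting will differ, in which direction and by how much cannot be learned from the protocol. The tabulated shifts show sensitivity only. They rest on assumed reading counts, assumed ICCs, normal readings and independence within a patient once the patient's level is fixed; correlation between neighbouring readings would reduce them.

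The change is worth making because it is cheap, because a heart-rate measure free of charting frequency is already collected, and because the missing count cannot be put right from the form afterwards.

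**What to change.** **Heart rate.** Under Main outcomes, name mean nocturnal heart rate from the night 2 oximetry (or its night 3 repeat) as the main heart-rate comparison. Keep the highest heart rate from form 2a as a supporting measure of brief tachycardia. No new data are needed.

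**Blood pressure and temperature.** Keep the maxima, and keep the full week 1 window for temperature so that fever on days 4 to 7 still counts. Then do one of two things:

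- take each maximum only from readings made at the same set times in both arms; or
- add to form 2a the number of readings behind each maximum and the days in hospital within the window, so that unequal measurement can be detected and allowed for.

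**Cost.** A nocturnal mean misses short daytime episodes, which is why the maximum stays alongside it. Form 2a gains one or two entries under the second option. The first option needs set reading times agreed with the wards.

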**CT /MRI diagnosis (please tick one of the boxes)**

- **Cerebral infarct**
- **Primary intracerebral haemorrhage**
- **Subdural haemorrhage**
- **Subarachnoid haemorrhage**
- **Brain tumour**
- **Head scan not performed**
- **Other (please specify) _______________________________**

**Final diagnosis**

**(Please make a final diagnosis using the clinical presentation, time course, head scan. Tick only one of the boxes)**

- **Ischaemic stroke**
- **TIA**
- **Primary intracerebral haemorrhage**
- **Cerebrovascular accident without CT confirmation of aetiology**
- **Other (Please specify) _____________________________**

For patients who were incompetent to sign consent at recruitment:

Competent to sign today? Yes No

If yes, explain study again and ask patient to sign form.

**Stroke Oxygen Study**

**Week 1 (Assessment form 2 b)**

Name Randomisation no

**Scandinavian Stroke Scale**

**(tick one box in each group, for items marked with* score the affected side)**

**Consciousness:**

- **6** fully conscious
- **4** somnolent,

can be awaked to full consciousness

- **2** reacts to verbal command,

but is not fully conscious

**Orientation:**

- **6** correct for time, place and person
- **4** two of these
- **2** one of these
- **0** completely disorientated

**Speech:**

- **10** no aphasia
- **6** limited vocabulary or incoherent speech
- **3** more than yes/no, but not longer sentences
- **0** only yes/no or less

**Facial palsy:**

- **2** none/dubious
- **0** present

